### Interim analyses and patient safety

A DSMB will be installed prior to the start of the study. The DSMB will meet and review the progress and acquired data. Interim analyses for the DISTINCT-1 trial and DISTINCT-3 trial are planned after 25%, 50% and 75% of the target number of subjects have been recruited and completed a 90-day follow-up. The DISTINCT-1 trial will be terminated when the lower limit of a two-sided 95% CI for the VTE incidence estimates in either of the two study groups exceeds 0.75%. In the DISTINCT-3 trial, we will test superiority using the O’Brien-Fleming alpha spending function to control the type I error; that is, we will perform a two-sided test, where superiority will be concluded in case the absolute value of the test statistic exceeds the boundary level of 4.084, 2.888 and 2.358 for the 25%, 50% and 75% interim analyses, respectively. In the superiority analysis, at the end of the study (after inclusion of the planned number of participants), superiority will be concluded if the absolute value of the test statistic exceeds the boundary level of 1.98. In addition, as a main safety rule, the absolute risk for major bleeds must not exceed the absolute risk for symptomatic VTE in either of the two treatment arms. The DSMB reviews the interim analyses and provides advice on the conduct of the trial to the trial steering committee.

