### Randomisation, blinding and treatment allocation

Approximately 2 weeks before surgery, patients will be randomised centrally by a clinical data management system (Castor Electronic Data Capture (EDC), V.2025.2.4.0 Amsterdam, the Netherlands). Randomisation within the DISTINCT-1 and DISTINCT-3 trials will be performed in a 1:1 ratio, using block randomisation with variable block sizes and stratified by study centre. This is an open-label study, meaning that patients and treating physicians will not be blinded to the intervention; however, outcome assessors will be. The DISTINCT-2 study is an observational study arm.

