#### Sample size calculation: DISTINCT-3 trial

By only including patients with a predicted VTE risk of >1.5%, a 90-day cumulative incidence of symptomatic VTE of 2.5% is expected in the control arm. This risk is based on the results from the development and validation studies of the TRiP(plasty) score.^18^ We expect that the intervention gives a relative risk reduction of 50% (ie, expected outcome in the intervention arm: 1.25%). This risk reduction was estimated from earlier dose-finding trials and our recently performed pilot study.^30^,^32^

At a two-sided alpha level of 0.05 and a power of 80%, 3694 patients would be necessary. To account for the interim analysis and thus testing against a slightly stricter statistical significance level at the final analysis, a total of 3748 patients are required (1874 per treatment arm). To account for a maximum dropout rate of approximately 9%, we aim to include 2050 patients in each arm, totalling 4100 patients.

For the DISTINCT-3 trial, we assume an increased relative major bleeding risk of 65% (from 0.5% to 0.83%) by increasing the thromboprophylaxis dose and duration. This estimate is based on results from earlier trials and our pilot study.^30^,^32^

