#### DISTINCT-3 statistics

A primary modified ITT analysis and a secondary PP analysis will be performed. The overall cumulative incidences of symptomatic VTE and major bleeding between the control and the intervention groups will be compared, using a superiority analysis for the risk difference. The 95% CI for the absolute difference in event risks will be determined.

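### DISTINCT-3: with three interim looks, the stated boundaries ending in 1.98 give an overall two-sided type I error of 5.36%, not 5%

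*Protocol article*

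**What the plan says.** All references are to the protocol article.

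- *Sample size calculation: DISTINCT-3 trial* fixes the error rates: "At a two-sided alpha level of 0.05 and a power of 80%, 3694 patients would be necessary". The assumed risks are given as "a 90-day cumulative incidence of symptomatic VTE of 2.5% is expected in the control arm" and "expected outcome in the intervention arm: 1.25" per cent.
- The same section then raises the total to 3748 (1874 per arm), for this reason: "To account for the interim analysis and thus testing against a slightly stricter statistical significance level at the final analysis". Allowing for about 9% dropout, the target is 4100.
- *Interim analyses and patient safety* plans looks at 25%, 50% and 75% of the target number with completed 90-day follow-up. It names an O'Brien-Fleming alpha spending function as the means of controlling the type I error in a two-sided test. The interim values are a "boundary level of 4.084, 2.888 and 2.358 for the 25%, 50% and 75% interim analyses, respectively".
- For the end of the study it states that "superiority will be concluded if the absolute value of the test statistic exceeds the boundary level of 1.98".

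**The concern.** A group-sequential design controls the overall error only if its interim and final critical values are derived together. Here they appear not to be. The three interim values follow one pattern, and the final value is lower than that pattern or the named spending function would give. The article also speaks of the interim analysis in the singular when it inflates the sample size, but plans three.

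At stake is the decision threshold of the confirmatory superiority test. A final test statistic between 1.98 and about 2.02 in absolute value would lead to a claim of superiority that the stated 5% level does not support.

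**Working it through.** **Inputs from the article.** Two-sided alpha 0.05; power 80%; risks 2.5% and 1.25%; 1:1 allocation; looks at 25%, 50%, 75% and 100%; boundaries 4.084, 2.888, 2.358 and 1.98; 1874 per arm.

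**Assumption.** Information is proportional to the number of patients, so the test statistics at fractions t_i < t_j are jointly normal with correlation sqrt(t_i/t_j).

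**Step 1: reproduce the sample size.** The pooled two-proportion formula per arm is

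n = [z_a × sqrt(2p(1−p)) + z_b × sqrt(p1(1−p1) + p2(1−p2))]² / (p1 − p2)²

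with p1 = 0.025, p2 = 0.0125 and p = 0.01875. Then 2p(1−p) = 0.036797, p1(1−p1) + p2(1−p2) = 0.036719, p1 − p2 = 0.0125 and z_b = 0.8416.

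- z_a = 1.96: total 3694.5 (stated 3694).
- z_a = 1.98: total 3747.5, rounded up to 3748 (stated 3748).

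Both stated figures reproduce, the second with 1.98 as the critical value.

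**Step 2: type I error of the stated boundaries.** Recursive numerical integration under the null gives these cumulative two-sided crossing probabilities:

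| Look | Boundary | Cumulative error |
|---|---|---|
| 25% | 4.084 | 0.00004 |
| 50% | 2.888 | 0.0039 |
| 75% | 2.358 | 0.0198 |
| 100% | 1.98 | 0.0536 |

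A simulation of 20 million paths gives 0.05364 (standard error 0.00005). A binomial simulation with the pooled test at 1874 per arm gives 5.3% for common risks from 1.25% to 2.5%.

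**Step 3: could rounding explain it?** No. A final value of 1.975 gives 5.41%, and 1.985 gives 5.31%.

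**Step 4: which design do the values belong to?** Multiply each interim boundary by the square root of its fraction:

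- 4.084 × sqrt(0.25) = 2.042
- 2.888 × sqrt(0.50) = 2.042
- 2.358 × sqrt(0.75) = 2.042

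This is the classical O'Brien-Fleming shape, whose own final value would be 2.042. Complete sets for comparison:

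| Set | 25% | 50% | 75% | 100% | Overall error |
|---|---|---|---|---|---|
| Stated | 4.084 | 2.888 | 2.358 | 1.98 | 5.36% |
| Stated shape carried to the end | 4.084 | 2.888 | 2.358 | 2.042 | 4.78% |
| Stated interims, final value solved for 5% | 4.084 | 2.888 | 2.358 | 2.018 | 5.00% |
| O'Brien-Fleming-type spending function | 4.333 | 2.963 | 2.359 | 2.014 | 5.00% |
| Classical O'Brien-Fleming, four analyses | 4.049 | 2.863 | 2.337 | 2.024 | 5.00% |

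By the 75% look the stated values have spent 0.0198, against 0.0193 for the spending function. The excess therefore arises at the final analysis.

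**Step 5: power with 1874 per arm.**

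- Group-sequential, final value 1.98: 80.7%.
- Group-sequential, final value 2.018 or the spending-function set: 79.7% to 79.9%, depending on the set and the variance estimate.
- Fixed-sample pooled formula with 2.018: (0.0125 × sqrt(1874) − 2.018 × sqrt(0.036797)) / sqrt(0.036719) = 0.804, which is 78.9%.

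To reach 80% with the stated interims and 2.018, the group-sequential inflation factor gives 1.0212 × 3694 ≈ 3772 patients. The fixed-sample formula gives about 3850.

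**The case against.** The strongest reply is that the excess is only 0.36 percentage points, that the interim values do no harm in themselves, and that power barely changes. All of that stands, and it limits the size of the point. It does not remove it: the article prints the exact thresholds and claims error control that they do not deliver. Because the numbers are stated, a fuller analysis plan cannot cure them by adding detail. The major-bleeding safety rule does not offset the excess either, since it is not described as a binding futility boundary.

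A reader might infer four stronger things that the documents do not support.

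- *That 1.98 was carried over from a design with a single look at 50%.* The final value there is 1.977, and the singular wording in the sample size section fits. This remains an inference; the article does not say where 1.98 comes from.
- *That a final statistic between 1.98 and 2.018 would be a false positive.* It would only have crossed a boundary that is slightly too lenient.
- *That the confidence interval will contradict the test.* The DISTINCT-3 statistics section says "The 95% CI for the absolute difference in event risks will be determined" and gives no multiplier. Reporting a nominal interval beside a group-sequential test is not in itself an error.
- *That the trial is materially undersized.* Step 5 of the working shows that it is not.

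**Conclusion.** The point holds. The stated boundaries for the DISTINCT-3 superiority test have an overall two-sided type I error of 5.36% against the stated 5%, and the cause is the final value of 1.98. With the stated interim values it should be about 2.018. That 3748 was computed from 1.98 is not stated, but the figure reproduces exactly that way.

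The mismatch between the interim values and the named spending function is mainly a matter of labelling, though the description and the numbers need to agree.

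The result rests on looks at exactly 25%, 50% and 75% and on information proportional to patients. The excess is small, but it should be corrected because it affects the decision rule for the primary efficacy outcome and the correction costs almost nothing.

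**What to change.** 1. In *Interim analyses and patient safety*, replace the four boundaries with one coherent set, by either route:
   - 4.333, 2.963, 2.359 and 2.014, which is the named O'Brien-Fleming-type spending function at the planned fractions, to be recomputed at the fractions actually observed; or
   - the three stated interim values with a final value of 2.02 (overall error 4.98%). The method description must then be reworded, because this set is not the named spending function.
2. In *Sample size calculation: DISTINCT-3 trial*, refer to three interim analyses. Restate that 1874 per arm gives about 79.8% group-sequential power, or 78.9% if the corrected final value of 2.018 is put into the fixed-sample formula. State which method is used.
3. Either accept power just under 80%, or raise the evaluable total from 3748 to about 3772 by group-sequential inflation (with the stated interims and 2.018), before the dropout allowance.

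The cost is one or more critical values and some wording, with few or no extra patients. The change should be dated before the first DISTINCT-3 interim analysis, so that it cannot be read as a response to the data.

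### The DISTINCT-3 main safety rule compares bleeding with VTE inside one arm, so under the planned rates it is breached in about 28% of trials, and more often the better the drug prevents VTE

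*Protocol article*

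**What the plan says.** The rule is in the protocol article under Interim analyses and patient safety, directly after the DISTINCT-3 superiority boundaries. It is called a main safety rule and reads: "the absolute risk for major bleeds must not exceed the absolute risk for symptomatic VTE in either of the two treatment arms". No confidence limit, test, minimum event count or consequence is attached. The same section ends a different trial, DISTINCT-1, on the lower limit of a two-sided 95% CI, and gives the DISTINCT-3 efficacy test exact boundaries. The looks are "planned after 25%, 50% and 75% of the target number of subjects have been recruited and completed a 90-day follow-up". The DSMB reviews the interim results and advises the trial steering committee.

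The planned rates are under Sample size calculation: DISTINCT-3 trial. For VTE, "a 90-day cumulative incidence of symptomatic VTE of 2.5% is expected in the control arm", and for the other arm, in per cent, "expected outcome in the intervention arm: 1.25". Major bleeding is assumed to rise from 0.5% to 0.83%. The target is 2050 per arm (4100), of whom 1874 per arm (3748) are needed before dropout.

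**The concern.** If the intervention does exactly what the plan hopes, its own arm has VTE of 1.25% and bleeding of 0.83%, a gap of 0.42 points. At the first look that is about 6 events against 4, an order that chance easily reverses.

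The rule also points the wrong way. Preventing more VTE narrows the gap and makes a breach likelier. Preventing none leaves VTE at 2.5%, a gap of 1.67 points, so a sizeable excess of bleeding can pass without a signal. What matters for net harm is bleeds caused against VTEs prevented. Both are differences from control, and the rule uses neither.

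At stake is the quality of the signal the DSMB receives: frequent alarms about a regimen performing to plan, and reassurance about one that adds bleeding without benefit.

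**Working it through.** **Inputs.** Control: VTE 2.5%, bleeding 0.5%. Intervention: VTE 1.25%, bleeding 0.83%. Target 2050 per arm, allocation 1:1, looks at 25/50/75%, final boundary 1.98. All are from the protocol article.

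**The plan's own sample size first.** The article says "At a two-sided alpha level of 0.05 and a power of 80%, 3694 patients would be necessary". With pooled variance, n per arm = [z(α/2)·√(2p̄(1−p̄)) + z(β)·√(p₁(1−p₁) + p₂(1−p₂))]² / (p₁−p₂)², with p̄ = 0.01875.
- Critical value 1.96: n = 1847.2, total 3694 (3696 if each arm is rounded up).
- Critical value 1.98: n = 1873.8, so 1874 per arm and 3748 in total, as stated.

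The rates are therefore read as the plan uses them.

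**First look, exact.** 25% of 2050 is 512 per arm. Expected VTEs: 512 × 0.0125 = 6.4. Expected bleeds: 512 × 0.0083 = 4.2. With V and B independent binomial counts, P(B > V) = Σₖ P(V = k)·P(B > k) = 20.5%.

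**All looks.** Cumulative binomial counts were simulated at 512, 1025 and 1537 per arm (1,000,000 trials per scenario). A breach means that bleeds exceed VTEs in either arm.
- Intervention arm as planned: 20.5%, 14.6% and 10.7% at the three looks.
- Either arm, at any look: 28.0%. The intervention arm alone gives 27.9%; the control arm breaches in 0.15% of trials at the first look and almost never later.
- With 1874 per arm: 29%.

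**How the rule responds.** Control stays at 2.5% and 0.5%, total 3.0%. Net is intervention minus control in VTE plus bleeding, in percentage points, with equal weights.

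| Intervention VTE | Intervention bleeding | Net | Breach at any look |
|---|---|---|---|
| 0.83% | 0.83% | 1.66 − 3.0 = −1.34 | 63% |
| 1.0% | 0.83% | 1.83 − 3.0 = −1.17 | 47% |
| 1.25% (plan) | 0.83% | 2.08 − 3.0 = −0.92 | 28% |
| 1.75% | 0.83% | 2.58 − 3.0 = −0.42 | 8.4% |
| 2.5% (no benefit) | 0.83% | 3.33 − 3.0 = +0.33 | 1.3% |
| 2.5% | 1.0% | 3.5 − 3.0 = +0.50 | 2.6% |
| 2.5% | 1.5% | 4.0 − 3.0 = +1.00 | 12.5% |
| 2.5% | 2.0% | 4.5 − 3.0 = +1.50 | 36% |

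With bleeding fixed at 0.83%, the breach rate falls steadily as the benefit disappears. With no benefit, it passes the as-planned 28% only as bleeding approaches four times control.

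**A between-arm comparison, as illustration.** The alert is z > 3 on the difference in major bleeding (pooled variance), at the same looks.

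| Intervention VTE / bleeding | Printed rule | z > 3 on bleeding difference |
|---|---|---|
| 1.25% / 0.83% (plan) | 28% | 3% |
| 2.5% / 0.83% | 1.3% | 3% |
| 2.5% / 1.5% | 12.5% | 44% |
| 1.25% / 1.5% | 81% | 44% |

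The z rule does not use VTE, so its rate depends on the bleeding rates alone.

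**The case against.** **A breach has no stated consequence.** This stands. The article says DISTINCT-1 will be terminated under its rule, but gives no such consequence here. A reader might set the 28% beside the 80% power and infer that over a quarter of successful trials would be lost. The document does not support that: the figure is the chance of an observation that calls for DSMB judgement.

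**A charter may add a confidence limit.** The article prints no estimator. If a normal-approximation criterion (z > 1.96 on bleeds minus VTEs within the arm) were required, the breach rate under plan would drop to about 0.6%. But no such limit is printed, and adding one would cure only the false alarms. The comparison would still become harder to satisfy as VTE falls.

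**It is not the only safeguard.** This also stands. The DSMB sees the accumulating data and may advise freely, and major bleeding is compared between arms in the DISTINCT-3 analysis. One cannot infer that patients are left unprotected. The point is confined to the rule labelled as main.

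**It is a simple net-benefit heuristic.** The intention is recognisable, but as planned the drug prevents 2.5 − 1.25 = 1.25 points of VTE for 0.83 − 0.5 = 0.33 points of bleeding, and the rule looks at neither difference.

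**A between-arm bound is not better everywhere.** Correct. With no VTE benefit and 0.83% bleeding, z > 3 also fires only about 3% of the time. With the planned benefit and 1.5% bleeding, the printed rule is the more sensitive, 81% against 44%.

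**Conclusion.** The concern holds as a flaw in the printed monitoring rule. Under the plan's own rates the rule raises a false alarm in about 28% of trials (29% with 1874 per arm). The rate climbs to 63% as the drug becomes more effective, and is 1.3% to about 12.5% when the drug prevents nothing and bleeding is between 0.83% and 1.5%.

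Two stronger readings are tempting. That the rule never catches a useless, harmful drug is wrong, because at 2.0% bleeding it fires 36% of the time. That it also governs DISTINCT-1 is not supported, because the sentence follows the DISTINCT-3 boundaries and the article gives no major bleeding rate for DISTINCT-1 from which to compute.

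Assumptions: absolute risk means the observed cumulative proportion; VTE and bleeding are independent within a patient; a breach at any of the three interim looks counts; early stopping for superiority is ignored. The direction of the effect follows from the form of the rule and not from the simulation.

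This should be corrected, but it does not threaten the primary analysis and ranks below a must-fix.

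**What to change.** Replace or supplement the sentence with a between-arm monitoring guideline for DISTINCT-3 that:
- sets the intervention-minus-control difference in major bleeding against a pre-stated bound at each look;
- shows beside it the between-arm difference in VTE plus major bleeding, with its CI, so that a lack of VTE benefit is visible;
- states the false-alarm rate under the planned rates;
- says that the guideline is advisory and informs the DSMB's recommendation.

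The DSMB and steering committee choose the bound; z > 3 above only shows how to report its properties.

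The cost is wording in the protocol and DSMB charter, with no added patients or data. The downsides are a rule that is less simple to state and, with a bound like the one illustrated, some loss of sensitivity when the VTE benefit is as planned and bleeding is 1.5%. The change is most credible before the first DISTINCT-3 look at 25% of 4100 = 1025 patients. The article reports just over 850 enrolled across all three studies, so that look had not been reached when it was written.

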### Patient and public involvement

A patient representative is part of the trial steering committee. As such, patients are involved in all aspect this study.

## Ethics and dissemination

This study will be conducted in accordance with the Declaration of Helsinki and applicable guidelines, laws and acts. The study is registered at ClinicalTrials.gov (NCT06581965) prior to the start of participant inclusion.

Ethical approval is provided by the Medical Research Ethics Committee Leiden-Den Haag-Delft (MREC LDD; EU trial number 2023-510186-98). MREC LDD will be notified in case of any substantial amendments; additionally, in case of an important protocol modification, the trial registry will be updated. Trial results will be published in international peer-reviewed journals regardless of the study findings.

Data will be collected in accordance with the General Data Protection Regulations. After data collection and data cleaning are completed, de-identified data will be registered in a repository and made available for further research on reasonable request to the corresponding author.
